## Abstract

**Introduction:**

A retained placenta is diagnosed when the placenta is not delivered following delivery of the baby. It is a major cause of postpartum haemorrhage and treated by the operative procedure of manual removal of placenta (MROP).

**Methods and analysis:**

The aim of this pragmatic, randomised, placebo-controlled, double-blind UK-wide trial, with an internal pilot and nested qualitative research to adjust strategies to refine delivery of the main trial, is to determine whether sublingual glyceryl trinitrate (GTN) is (or is not) clinically and cost-effective for (medical) management of retained placenta. The primary clinical outcome is need for MROP, defined as the placenta remaining undelivered 15 min poststudy treatment and/or being required within 15 min of treatment due to safety concerns. The primary safety outcome is measured blood loss between administration of treatment and transfer to the postnatal ward or other clinical area. The primary patient-sided outcome is satisfaction with treatment and a side effect profile. The primary economic outcome is net incremental costs (or cost savings) to the National Health Service of using GTN versus standard practice. Secondary outcomes are being measured over a range of clinical and economic domains. The primary outcomes will be analysed using linear models appropriate to the distribution of each outcome. Health service costs will be compared with multiple trial outcomes in a cost-consequence analysis of GTN versus standard practice.

**Ethics and dissemination:**

Ethical approval has been obtained from the North-East Newcastle & North Tyneside 2 Research Ethics Committee (13/NE/0339). Dissemination plans for the trial include the Health Technology Assessment Monograph, presentation at international scientific meetings and publication in high-impact, peer-reviewed journals.

**Trial registration number:**

ISCRTN88609453; Pre-results.

Strengths and limitations of this studyPragmatic randomised placebo-controlled double-blind UK-wide trial to determine whether sublingual glyceryl trinitrate is (or is not) clinically and cost-effective for (medical) management of retained placenta.Inclusion of clinical, patient-sided, safety and economic outcomes with minimal exclusion criteria.Pragmatic approach to obtaining consent and good clinical practice (GCP)-training to facilitate recruitment in the emergency setting.Fully adaptive group sequential design.Inability to differentiate whether a placenta is adherent or trapped prior to administration of study drug.

## Introduction

### Background

A retained placenta (RP) is diagnosed when the placenta is not delivered within 30 or 60 min after delivery of the baby following active or physiological management of the third stage of labour, respectively^1^ and is a major cause of postpartum haemorrhage.^2 3^ The incidence of retained placenta is rising in the UK due to changes in maternal demographics, increased intrapartum interventions and operations involving exploration of the uterine cavity including surgical termination of pregnancy and dilation and curettage.^4^ Retained placenta currently affects approximately 2% of vaginal deliveries^4^ which equates to nearly 11 000 women per annum in the UK. Following failure of active or physiological management, the National Institute of Health and Care Excellence recommends that retained placenta should be treated by the operative procedure of manual removal of placenta (MROP).^1^ This procedure requires skilled personnel, an operative environment and, compared with spontaneous placental delivery, has its own attendant risks, including bleeding^3^ and infection.^5^ There is often a delay in undertaking the operation, which leads to further haemorrhage,^6^ and the procedure itself is costly in terms of staff time. Furthermore, the infrastructure required for this operative intervention is not available in all delivery settings, and the invasive nature of this procedure has the potential to delay or interrupt mother–baby bonding in the immediate postpartum period. To reduce the number of women requiring MROP, there is therefore a need for new (and effective) medical treatments for retained placenta. The reduction in operative interventions would potentially have cost benefits for the National Health Service (NHS) and also for women in terms of increased satisfaction, less separation between mother and baby immediately after birth and reduced morbidity.

### Rationale for study

Observational studies along with results from small randomised controlled trials have suggested that nitric oxide donors including glyceryl trinitrate (GTN) given intravenously might be effective for the management of retained placenta with success rates ranging between 94% and 100%.^7–10^ Although intravenous GTN appears to be efficacious for retained placenta in these small studies, this route of administration is not practical in all settings and intravenous administration causes unacceptable side-effects including symptomatic hypotension at higher doses.^3^ More recently, sublingual administration has been trialled, with studies reporting experience with sublingual GTN tablet and spray. Using a sublingual GTN tablet, two small studies suggest a beneficial effect of sublingual GTN tablet; however, a third larger study does not (ISRCTN34755982; 37.3% vs 20.4%; GTN vs placebo; p>0.05; n=105 women).^11^ The alternative preparation for sublingual administration is GTN spray.^12^ Compared with the tablet preparation, sublingual GTN spray has several advantages including stability at room temperature, significant reduction in latency of onset with onset beginning at 30–45 s, peaking at 90–120 s and lasting up to 5 min,^13–15^ and fewer objective and subjective side-effects.^16^ GTN spray is an accepted obstetric management in other scenarios where rapid tocolysis is required such as uterine relaxation for release of a trapped head in breech delivery or at caesarean section.^12^ Furthermore, anecdotal reports suggest that GTN spray may also have a use in management of retained placenta.^12^

To summarise, although a growing body of evidence supports GTN use for the treatment of retained placenta, much of this evidence is based on anecdotal case reports or clinical studies which are non-randomised, do not include a placebo arm and are underpowered. There is therefore a need to undertake a well-designed, randomised, placebo-controlled, double-blind pragmatic group sequential UK-wide (GOT-IT trial) to definitively determine whether sublingual GTN is (or is not) clinically and cost-effective for management of retained placenta.

### Study objectives

The aim of this placebo-controlled, double-blind, pragmatic group sequential UK-wide trial is to determine the effectiveness and cost-effectiveness of GTN for treating retained placenta and avoiding MROP.

The hypothesis being tested is that sublingual GTN spray is clinical and cost effective in treating retained placenta after vaginal delivery, reducing the need for MROP following failure of current management.

The primary objectives are to: (1) determine the clinical effectiveness of sublingual GTN in treating retained placenta and avoiding MROP in women with vaginal delivery following failure of current management (clinical domain), (2) determine the side-effect profile for GTN given to treat retained placenta (safety domain), (3) assess patient satisfaction with GTN given for retained placenta (patient-sided domain) and (4) assess the net costs (or cost savings) to the NHS of using GTN for the treatment of retained placenta compared with standard practice (economic domain).

The secondary objectives are to assess NHS costs in relation to the primary outcome and range of secondary outcomes which are expected to differ between the two arms of the trial, using a cost-consequence balance sheet approach.

The trial contained an internal pilot, which commenced in October 2014 and was completed in April 2015. The aim of this internal pilot, which recruited from eight sites across the UK, was to provide reassurance on all the trial processes, including recruitment, consent, randomisation, delivery of treatment and follow-up assessments to ensure that all were running smoothly. Recruitment to the substantive trial is ongoing and is due to finish in September 2017.

A nested qualitative study was undertaken during the internal pilot to adjust strategies to (1) maximise recruitment into the main trial, (2) refine the recruitment and consent pathway and (3) ensure staff are given appropriate training and support to help promote the successful delivery of the main trial. In-depth qualitative interviews were undertaken with staff (n=27) involved in trial recruitment, consenting and/or trial delivery and with trial recruits (n=22) within, when possible, 4 weeks of randomisation. The results of the qualitative research have been published and have informed the delivery of the main trial.^17 18^

## Methods and analysis

### Study design

This is a placebo-controlled, double-blind, pragmatic group sequential UK-wide trial to determine the effectiveness of GTN for treating retained placenta and avoiding MROP. Women are identified as being potentially eligible for the trial if, following vaginal birth, they have a retained placenta and are at risk of needing a MROP after failure of current management of the third stage of labour. If eligible for the trial, women are treated with either the study drug or a placebo in a double-blind fashion. Following administration of the study medication, if the placenta still remains undelivered after 15 min, the treating clinician determines ongoing clinical management as per standard care.

The prespecified group sequential monitoring plan requires the Data Monitoring Committee to look at accumulating unblinded data on five occasions. The Data Monitoring Committee is using the results of these analyses to advise the Trial Steering Committee on adapting the trial design to either (1) stop prematurely for futility (no prospect of establishing a treatment effect of at least 10%) or (2) stop prematurely if proof beyond a reasonable doubt is established that there is a convincing treatment benefit of at least 10%. Assuming the trial recruits to its maximum size, we are aiming to recruit 1100 participants (maximum number randomised 1086, with the uplift to 1100 to account for a small allowance for withdrawal of consent or other rare loss to follow-up) over 42 months.

### Study population

#### Setting

We are recruiting women from delivery wards in UK maternity hospitals. The delivery wards are of varying size and location ensuring the results of the trial will be generalisable to the UK. At present, recruitment is being undertaken in 28 sites across the UK.

#### Selection of participants

As is standard practice, clinicians are undertaking the initial eligibility screening. Women are identified as being potentially eligible for the trial if, following vaginal birth, they have a retained placenta and are at risk of needing a MROP after failure of current management of the third stage of labour, defined as the placenta remaining undelivered after (1) 30 min of active management or (2) 60 min of physiological management plus a further 30 min of active management of the third stage of labour.

#### Planned inclusion and exclusion criteria

All women will be considered for the trial who have RP after vaginal birth following failure of current management (defined as a third stage of labour lasting more than (1) 30 min after active management or (2) 60 min following physiological followed by 30 min of active management. In addition, they should also satisfy the following inclusion criteria. Should a woman have any of the exclusion criteria, they will not be invited to participate in the trial.

Women are eligible for inclusion if they are:Aged ≥16 yearsVaginal delivery (including women with a previous caesarean section and an instrumental vaginal delivery in the delivery room)>14 weeks gestationHaemodynamically stable, defined as having a heart rate ≤119 beats per minute and a systolic blood pressure of >100 mm Hg

##### Exclusion criteria

Women are excluded if they have one or more of the following:Unable to give informed consentSuspected placenta accreta/increta/percretaMultiple pregnancyAllergy or hypersensitivity to nitratesConsumption of alcohol in the last 24 hoursConcomitant use of phosphodiesterase inhibitorsInstrumental vaginal delivery in theatreContraindications to nitrates including severe anaemia, constrictive pericarditis, extreme bradycardia, incipient glaucoma, glusose-6-phosphate dehydrogenase–deficiency, cerebral haemorrhage and brain trauma, aortic and/or mitral stenosis, angina caused by hypertrophic obstructive cardiomyopathy, circulatory collapse, cardiogenic shock and toxic pulmonary oedema

### Recruitment and study procedures

#### Identifying participants

Recruitment was initiated in October 2014 and is currently ongoing in the delivery wards of 28 UK maternity hospitals. Recruitment is scheduled to conclude when 1100 subjects are recruited to the trial.

We initially followed the Royal College of Obstetrics and Gynaecology best practice recommendations for recruitment and obtaining consent for intrapartum research studies.^19^ These recommendations were based on the work by Vernon *et al*,^20^ who developed a consent pathway for women with retained placenta who were recruited to the RELEASE trial of umbilical vein oxytocin for RP.^21^ We refined this pathway in light of our qualitative research^17 18^ so that the consent and recruitment pathways were tailored to the specific requirements of this trial. In brief, where possible, outline information about the trial (including researcher contact details) is made available to women antenatally, particularly those identified as being at high risk of retained placenta, for example, maternal age >30 years, preterm birth and stillbirth.^22^ More detailed information is available in antenatal clinics, on labour wards and the study website with information posters in the hospital reception areas and antenatal clinics. Following diagnosis of a retained placenta, a clinician or midwife who has received GOT-IT study training (which has sponsor-approved GCP-training embedded within it) invites women to participate in the trial, provides an explanation of the study and gives potential participants an abbreviated and/or full version of the patient information sheet.

#### Informed consent

The patient information leaflets explain that the trial is investigating whether sublingual GTN spray is useful for treating retained placenta. If a woman wishes to participate then written or verbal consent is obtained. If verbal consent is obtained, this is followed up by written consent as soon as possible in the postnatal period. Such an approach has been endorsed by the Royal College of Obstetricians and Gynaecologists in recent guidance about obtaining consent in perinatal research where consent is time critical in which it is stated that ‘[in acute circumstances]…provision of antenatal information to women with brief oral consent at the time of the complication is appropriate. Full written consent is then obtained at a later stage’.^23^ Permission is sought to inform the woman’s general practitioner that she is taking part in this trial. Due to the emergency nature of the condition (retained placenta), women are eligible to take part if they fulfil the inclusion criteria, understand what trial participation involves and give fully informed consent. A minimum time period is not feasible for trial consideration by potential participants. If a woman cannot give informed consent (eg, due to incapacity), she is not eligible for participation.

#### Randomisation and allocation

The study drug is a metered dose sublingual spray containing 400 µg/dose of GTN and a matching placebo spray. The formulation consists of GTN, peppermint oil BP (88%), 1,1,1,2-tetrafluoroethane (HFA) and ethanol BP (96%). The placebo is identical to the active product minus the GTN. Both the study drug and the matching placebo are manufactured by Pharmasol Limited and labelled by Sharp Clinical Services (UK) Limited.

Study drugs are kept on the delivery suite and are provided to site pharmacies in prepacked randomised permuted blocks. After consent of each participant, the investigator or trained clinical practitioner randomises eligible and consenting women to one of the two study groups by taking the next box off the shelf. After priming the pump and demonstrating its use, the clinician gives the study drug to the women to self-administer. The study is double-masked, so neither the participant, investigator nor trained clinical practitioner know which treatment has been allocated. The boxes are numbered and labelled so that the identity of the drug can be determined later. The number on the box is logged in the study database. Breaking of the study masking is only performed where knowledge of the treatment is absolutely necessary for safe management of the patient.

A central emergency unblinding interactive voice response system is operated by the Centre for Healthcare Randomised Trials (ChaRT) in Aberdeen. Only senior clinicians can unblind trial participants. The name of the clinician requesting the unblinding, the reasons for it and notification of any unblinding is sent to the chief investigator via email. Reasons for unblinding are recorded in the participant’s sources documents and in the Investigator Site Master File. Unless there is a clinical requirement, masking will not be broken until after all study data entry is complete, the validity of the data is checked, all queries resolved and the patient populations agreed.

#### Administration of study intervention

Women who have a retained placenta after vaginal birth or miscarriage following failure of management of the third stage of labour (failure of active management defined as the third stage lasting more than 30 min and failure of physiological management defined as the third stage lasting more than 60 min, plus a further 30 min of active management) are considered for eligibility for the trial.

Baseline observations (maternal blood pressure (mm Hg) and heart rate (beats per minute)) are taken prior to study drug administration to confirm that the woman fulfils the haemodynamic inclusion criteria (heart rate ≤119 bpm and systolic blood pressure >100 mm Hg) for trial entry.

Following confirmation of eligibility, women self-administer two puffs of either GTN (800 µg) or placebo spray as a once-only, sublingual intervention via a pump spray. Maternal temperature and a blood sample to measure haemoglobin are measured at baseline. Heart rate, systolic blood pressure and temperature (^o^C) are recorded at 5 and 15 min after administration of the study drug.

Sublingual GTN is maximally effective in causing uterine and cervical relaxation by 5 min postadministration. Thus, if spontaneous delivery of the placenta is going to occur, we expect this to happen around 5 min after drug administration. If spontaneous placental delivery has not occurred, a further attempt to deliver the placenta by controlled cord traction is made. If the placenta remains undelivered 15 min after administration of the treatment we think that it is highly unlikely that it will deliver spontaneously thereafter—we consider that any further delay risks haemorrhage. Thus, the decision that MROP is needed (primary clinical outcome) is made and the participant transferred to theatre for the definitive management of MROP as soon as possible. Additionally, if there are clinically significant side-effects (eg, haemorrhage, symptomatic maternal hypotension and/or tachycardia) before 15 min have elapsed after GTN/placebo treatment, the participant is transferred to theatre for immediate MROP.

#### Follow-Up procedures

On the first postnatal day, a haemoglobin sample is collected. A questionnaire relating to the woman’s perception of the study drug in relation to side-effects and patient satisfaction is also completed. A second questionnaire is sent by the Central Trial Office to participants at 6-week postdelivery. The questionnaire collects further information on patient-rated side-effects, patient-rated satisfaction and health economic resource use.

Women remain in the trial unless they are unable to continue for a clinical reason or choose to withdraw consent. All other changes in status, with the exception of formal withdrawal of consent, mean the participant will be followed up for all study outcomes whenever possible.

### Safety

The laws that govern reporting for clinical trials of investigational medicinal products (IMP) regulate safety reporting for the GOT-IT trial. Adverse events (AEs) may occur during or after participation in the trial.

#### Definitions

An AE is any untoward medical occurrence in a clinical trial participant which does not necessarily have a causal relationship with an IMP. Each AE is considered for severity, causality or expectedness and may be reclassified as a serious event.

An adverse reaction (AR) is any untoward and unintended response to the IMP which is related to any dose administered to that participant.

A serious adverse event (SAE) and serious adverse reaction (SAR) is any AE or AR that at any dose:results in death of the clinical trial participant;is life-threatening, defined as an event where the participant was at risk of death at the time of the event. It does not refer to an event which hypothetically might have caused death if it were more severe;requires inpatient hospitalisation or prolongation of existing hospitalisation;results in persistent or significant disability or incapacity;consists of a congenital anomaly or birth defect;results in any other significant medical event not meeting the criteria above.

A suspected unexpected serious adverse reaction (SUSAR) is any AR that is classified as serious and is suspected to be caused by the IMP, that it is not consistent with the information about the IMP in the summary of the medicinal product characteristics (SmPC).

#### Identifying AEs and SAEs

All AEs and SAEs are recorded from the time a participant signs the consent form to take part in the study until the 6-week postnatal outcome assessment point.

Participants are asked about the occurrence of AEs/SAEs prior to discharge from the hospital and in the 6-week postnatal questionnaire. Open-ended and non-leading verbal questioning of the participant are used to enquire about AE/SAE occurrence at discharge. The 6-week postnatal questionnaire also asks participants if they have seen their general practitioner, been admitted to hospital or been prescribed any medication. If there is any doubt as to whether a clinical observation is an AE, the event is recorded. AEs and SAEs are also identified via information from support departments, for example, laboratories.

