### Data collection and processing

#### Collection of outcome data

The primary clinical outcome (need for MROP, defined as the placenta remaining undelivered 15 min post-treatment and/or being required within 15 min of treatment due to safety concerns) is collected 15 min postadministration of the study drug. The primary safety outcome (measured blood loss between administration treatment and transfer to the postnatal ward/other clinical area) is recorded immediately prior to transfer from theatre to the postnatal ward or other clinical area (eg, labour ward high dependency). The primary patient satisfaction outcome is collected at 6 weeks by a self-completed satisfaction questionnaire and the primary economic outcome will be computed from costs incurred at initial management of retained placenta and management of further complications and self-reported health service usage and side-effects recorded from the postnatal patient questionnaires.

Outcome data are collected on an electronic case report form and paper-based questionnaires by research midwives and nurses who have been specifically trained in data collection for the trial. The electronic case record form comprises the following sections: baseline data, clinical observations and placenta delivery, first post natal day, discharge, 6-week postnatal check, safety events, discharge and follow-up questionnaires. Health service use in the 6 weeks following discharge is collected via a small number of resource use questions included in the postnatal questionnaires. Resource use will be evaluated using routine sources of nationally relevant unit costs. Women are permitted to receive all standard care medical treatments for postpartum complications including any given for medical management of retained placenta. Concomitant medications are recorded from 24 hours prior to signing of the consent forms until 24 hours after administration of the study drug. Analgesic or antibiotic medications are recorded from 24 hours prior to signing of informed consent until 6 weeks after administration of study drug.

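### The AE/SAE recording window opens when the consent form is signed, but women may be randomised and dosed on verbal consent and sign later

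*Protocol article*

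**What the plan says.** Four sections of the protocol article bear on this.

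- **Informed consent.** Two routes into the trial are open: "If a woman wishes to participate then written or verbal consent is obtained". For the verbal route, "If verbal consent is obtained, this is followed up by written consent as soon as possible in the postnatal period". No time limit is set for the signature.
- **Randomisation and allocation.** Allocation follows consent of either kind: "After consent of each participant, the investigator or trained clinical practitioner randomises eligible and consenting women". Self-administration of the spray comes next. No signature is required before dosing.
- **Identifying AEs and SAEs.** The safety window opens at the signature: "All AEs and SAEs are recorded from the time a participant signs the consent form to take part in the study". It closes at the 6-week postnatal assessment.
- **Collection of outcome data.** The two medication windows also start from the signature but end relative to dosing: "Concomitant medications are recorded from 24 hours prior to signing of the consent forms until 24 hours after administration of the study drug", and "Analgesic or antibiotic medications are recorded from 24 hours prior to signing of informed consent until 6 weeks after administration of study drug".

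**The concern.** Verbal consent is a planned route. The article lists its pragmatic approach to consent among the trial's strengths, and the emergency setting makes that route likely to be used. For a woman who takes it, the signature comes after the spray, so the written rule opens her AE/SAE window after the drug has acted. The article describes a fast and short effect: "Sublingual GTN is maximally effective in causing uterine and cervical relaxation by 5 min postadministration", with the Rationale for study putting the spray's duration at up to 5 min. Events caused by the drug are therefore most likely in the interval that the rule leaves out.

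Two things are at stake. First, the side-effect profile is one of the primary objectives. Second, the window covers all AEs and SAEs, so it feeds the later causality, expectedness and SUSAR assessments. A site that applies the sentence literally would see no duty to record an unlisted event between dosing and signature. A site that treats verbal consent as the start would record it. The rule should not leave room for both.

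**Working it through.** The article gives no figure to reproduce. The check places the windows on one time line.

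**Notation.** D is the time of dosing and S the time of signature. For a verbally consented woman who signs postnatally, S > D.

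**Inputs.**

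- AE/SAE window: from S to the 6-week assessment (Identifying AEs and SAEs).
- Concomitant-medication window: from S − 24 h to D + 24 h (Collection of outcome data).
- Analgesic and antibiotic window: from S − 24 h to D + 6 weeks (same section).
- Acute period: D to D + 15 min, the span of the post-dose observations, which "are recorded at 5 and 15 min after administration of the study drug" (Administration of study intervention).

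**AE/SAE window.** The part of the acute period before S is outside. For any S > D some of it is lost. Once S > D + 15 min, all of it is lost.

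**Concomitant-medication window.** Its start relative to dosing is (S − D) − 24 h. Dosing is inside as long as S − D ≤ 24 h, and the whole acute period is outside once S − D exceeds 24 h 15 min. Its length is (D + 24) − (S − 24) = 48 h − (S − D), which becomes negative beyond 48 h.

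The delays below are assumptions, since the article states none:

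| S − D | Acute period in AE/SAE window? | Medication window starts | Length of concomitant-medication window |
|---|---|---|---|
| 2 h | No | D − 22 h | 46 h |
| 23 h | No | D − 1 h | 25 h |
| 30 h | No | D + 6 h | 18 h |
| 50 h | No | D + 26 h | −2 h (empty) |

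The analgesic and antibiotic window starts at the same point, so it covers or misses the acute period in the same cases. At least 30 min of active management precedes dosing (Selection of participants). A drug given at the start of those 30 min therefore drops out once S − D exceeds 24 − 0.5 = 23.5 h.

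The two kinds of window thus behave differently. The AE/SAE window misses the acute period after any delay longer than 15 min. The medication windows keep dosing unless the delay is more than a day.

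**What is collected without reference to the signature.**

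- Heart rate, systolic pressure and temperature at 5 and 15 min (Administration of study intervention).
- Blood loss from administration to transfer, the primary safety outcome (Primary outcome measures).
- The listed expected events, which go into the case report form and to the Data Monitoring Committee (Recording AEs and SAEs). Most of them are also secondary outcomes.
- Patient-rated side effects, by questionnaire on the first postnatal day and at 6 weeks (Follow-Up procedures).
- SAEs that come to the investigator's knowledge, which must be reported within 24 hours with no condition about signature (Reporting of SAEs/SAR/SUSARs).

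Taking these away from what the literal AE/SAE window omits leaves unlisted AEs with onset between D and S, and SAEs or SUSARs in that interval, where the recording rule and the reporting rule disagree.

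**After the change.** If the window starts at the first consent of either form, its start is at or before D for every participant. The acute period is then covered whatever the value of S − D.

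**The case against.** The strongest reply is that the harms a reader would worry about first are captured anyway. Hypotension and tachycardia are picked up by the timed observations and a secondary outcome, haemorrhage by the primary safety outcome, and headache and similar complaints can be reported in the side-effect questionnaires. Women are also asked open questions about AEs before discharge, and doubtful observations are to be recorded. A dosed woman is a trial participant under the article's own AE definition, so the SAE reporting duty applies to her. The article also condenses a fuller protocol, in which the time point of consent may be defined. Nothing in the primary clinical outcome, the sample size or the interim monitoring is affected.

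Most of this stands, and it limits the consequences. It does not remove the contradiction. Asking about events later does not move the start of a window that is stated to cover all AEs and SAEs. The reporting rule does not cover non-serious events. The point concerns what the article states, so possible wording elsewhere does not settle it.

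Two stronger readings are tempting. A reader might infer that acute harms are under-counted in proportion to the share consenting verbally, so that the between-arm difference shrinks accordingly. That would need zero capture in every such woman, which the parallel collection contradicts, and a verbal-consent share and event rates that the article does not give. A reader might also infer that drugs given around treatment go unrecorded. The 24-hour look-back keeps dosing inside the window unless the signature comes more than 24 h later. The article reports no such delay and asks for the signature as soon as possible.

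**Conclusion.** The point holds in a limited form. The AE/SAE recording rule conflicts with the consent pathway. Followed literally, it excludes events that begin between dosing and signature in women who consented verbally. The practical loss is mainly unlisted AEs in that interval, together with an unclear duty to record SAEs and SUSARs there. The conclusion rests on reading the signature wording as written and on postnatal signature normally coming after dosing, which is what the consent section describes. The size of the gap cannot be calculated, because the article gives neither the proportion consenting verbally nor the delay to signature. The documents do not show that the named acute harms are missed or that the comparison between arms is biased. The medication windows are a lesser matter: mixing two anchors makes them shorten with delay, and dosing is lost only beyond 24 h. This is a cheap correction to safety wording and casts no doubt on the trial's main analysis.

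**What to change.** - **Main change.** Reword the start of the window under Identifying AEs and SAEs so that recording begins at consent in either form, verbal or written, whichever is first.
- **Women already treated.** The article describes recruitment as ongoing. For those dosed on verbal consent, check the hospital notes for events between dosing and signature that were not recorded.
- **Secondary tidy-up.** Under Collection of outcome data, anchor the look-back of both medication windows to study-drug administration, so that their coverage no longer depends on when the form was signed.

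The cost is a minor amendment, a short guidance note for completing the case report form, and a limited review of notes. No treatment rule or outcome definition changes.
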